## Abstract

**Background:**

Lung cancer is the most common cause of cancer related death worldwide. The majority of cases are detected at a late stage when prognosis is poor. The EarlyCDT®-Lung Test detects autoantibodies to abnormal cell surface proteins in the earliest stages of the disease which may allow tumour detection at an earlier stage thus altering prognosis.

The primary research question is: Does using the EarlyCDT®-Lung Test to identify those at high risk of lung cancer, followed by X-ray and computed tomography (CT) scanning, reduce the incidence of patients with late-stage lung cancer (III & IV) or unclassified presentation (U) at diagnosis, compared to standard practice?

**Methods:**

A randomised controlled trial of 12 000 participants in areas of Scotland targeting general practices serving patients in the most deprived quintile of the Scottish Index of Multiple Deprivation. Adults aged 50–75 who are at high risk of lung cancer and healthy enough to undergo potentially curative therapy (Performance Status 0–2) are eligible to participate. The intervention is the EarlyCDT®-Lung Test, followed by X-ray and CT in those with a positive result. The comparator is standard clinical practice in the UK. The primary outcome is the difference, after 24 months, between the rates of patients with stage III, IV or unclassified lung cancer at diagnosis. The secondary outcomes include: all-cause mortality; disease specific mortality; a range of morbidity outcomes; cost-effectiveness and measures examining the psychological and behavioural consequences of screening.

Participants with a positive test result but for whom the CT scan does not lead to a lung cancer diagnosis will be offered 6 monthly thoracic CTs for 24 months. An initial chest X-ray will be used to determine the speed and the need for contrast in the first screening CT. Participants who are found to have lung cancer will be followed-up to assess both time to diagnosis and stage of disease at diagnosis.

**Discussion:**

The study will determine the clinical and cost effectiveness of EarlyCDT®-Lung Test for early lung cancer detection and assess its suitability for a large-scale, accredited screening service. The study will also assess the potential psychological and behavioural harms arising from false positive or false negative results, as well as the potential benefits to patients of true negative EarlyCDT lung test results. A cost-effectiveness model of lung cancer screening based on the results of the EarlyCDT Lung Test study will be developed.

**Trial registration:**

NCT01925625. August 19, 2013

**Electronic supplementary material:**

The online version of this article (doi:10.1186/s12885-017-3175-y) contains supplementary material, which is available to authorized users.

## Background

Lung cancer is the world’s leading cause of cancer related mortality and a major source of morbidity [1]. It is often diagnosed at an advanced stage with 85% of patients undiagnosed until the disease is symptomatic [2]. Scotland has one of the highest rates of lung cancer in the world [3]. Around 2 460 men and 2 340 women are diagnosed with lung cancer in Scotland every year, which is 16% of the total UK cases, despite Scotland having only 8% of the UK’s population. Survival from lung cancer is poor with less than 9% of patients still alive at 5 years after diagnosis, due primarily to the late stage of presentation [4]. Early detection and diagnosis of cancer improves prognosis - the current 5-years survival rate is approximately 60% for stage I lung cancer but is only 1% for those with stage IV disease [5].

The first studies evaluating screening for lung cancer utilised chest X-ray and/or sputum cytology [6–9]. While these showed increased numbers of earlier-stage, resectable cancers and improved survival rates in the screened groups, not all studies were randomised. The lack of trial strength data means that differences in lung cancer mortality between those screened and those not are difficult to interpret.

The National Cancer Institute National Lung Screening Trial (NLST) reported that CT screening reduced lung cancer mortality by 20% [10]. This has led to a number of guidelines in the United States which advocate lung cancer screening with low dose CT [11]. However as a primary screening modality CT is expensive and leads to a significant percentage of false positives (>90% of nodules are found to be benign) [12]. There was a substantial increase in morbidity associated with further investigation. More recently the UK Lung Cancer Screening Trial reported successful early detection of lung cancer using low dose CT scans [13].

The EarlyCDT®-Lung Test is a novel Autoantibody(AAB) diagnostic test for the early detection of lung cancer allowing stratification of individuals according to their risk of developing lung cancer [14]. This could permit a targeted approach to CT scanning for early lung cancer detection which may be a more cost-effective and potentially less harmful approach to population screening.

The EarlyCDT®-Lung Test measures seven AABs; p53, NY-ESO-1, CAGE, GBU4-5, HuD, MAGE A4 & SOX2. It identifies 41% of lung cancers with a high specificity of 90% [14]. This compares to CT scanning, which when used alone as a prevalence screening test, identifies 67% of lung cancers developing over the following 12 months, but has a low specificity of around 49% [10]. The autoantibodies detected in the test have not been shown to vary with age, gender and ethnicity [15].

In a large group of patients (*n* = 3 376) with newly diagnosed lung cancers there was no difference in positivity rate for the test in early or late stage disease lung cancers, and this applied to all lung cancers [14, 16]. Thus, while autoantibodies are present in early stage they are not simply a biomarker of early stage disease. While preliminary data shows promise there is insufficient evidence, as yet, to support the introduction of this test for cancer screening or a case finding program.

Consequently, the primary research question is: ‘Does using the EarlyCDT®-Lung Test, followed by X-ray and CT scanning, to identify those at high risk of lung cancer reduce the incidence of patients with late-stage lung cancer (III & IV) or unclassified presentation (U) at diagnosis, compared to standard clinical practice?

### AIMS

To assess the effectiveness of the test in increasing early stage lung cancer detection, thereby reducing the rate of late stage (III/IV/U) presentation compared to standard practice; to assess the cost-effectiveness of the test compared to standard practice; to assess the impact of the test on quality of life, positive and negative affect, illness perceptions, lung cancer risk perception, health anxiety, lung cancer worry, subjective stress related to screening, smoking behaviour and health service use.

## Methods

### Design

This is a randomised controlled trial involving 12,000 participants recruited through primary care and community based recruitment strategies in Scotland. < h3 > Setting.

General practices who serve patients in the lowest quintile of deprivation in Scotland, as measured by the Scottish Index of Multiple Deprivation, will be targeted [17]. Additional recruitment will be attained through adverts, posters, flyers and community based interactions and may extend to other practices as needed to ensure reaching our recruitment targets. Potential participants can either be seen at their participating GP practice or at the local clinical research centre, or other appropriate clinical location.

### Participants

Adults aged 50–75 who have at least a 2% risk of developing lung cancer over the next 24 months will be eligible to participate [18]. These are defined as those who are, current or former cigarette smokers with at least 20 pack-years, or have a history of cigarette smoking less than 20 pack-years plus an immediate family history (mother, father, brother, sister, child) of lung cancer which gives an individual a personal risk similar to a smoking history of 20 pack years. Participants should be healthy enough to undergo radical treatment either by pulmonary resection or stereotactic radiotherapy.

#### Number of participants

We will recruit 12,000 participants, from approximately 170 general practices.

#### Inclusion criteria

Participant is willing and able to give informed consent for participation in the studyMale or female aged 50–75 yearsCurrent or Ex-smoker with at least 20 years pack historyLess than 20 years pack history but with family history of lung cancer in a 1st degree relative (mother, father, sister, brother, child)Eastern Co-operative Oncology Group Status: 0, 1 and 2 [19]

#### Exclusion criteria

History of any cancer other than non-melanomatous skin cancer and/or cervical cancer in situ.Complaining of symptoms suggestive of lung cancer within past 6 months i.e. haemoptysis or weight loss.Patients for whom the GP considers invitation to the study would cause undue distress.Patients with terminal disease.Patients on prolonged/continuous use (>3 months) of Cyclophosphamide.

#### Randomisation

Participants will be allocated to the intervention or comparison group during the recruitment visit (Visit 1) using a web-based randomisation system TRuST [20]. Randomisation will be stratified by site and minimised by age, sex and smoking history.

### Dates and duration of trial

01/08/2013–31/07/18 (60 months).

#### Identifying participants

Practices in the most deprived areas will be approached by facilitators in the Scottish Primary Care Research Network (SPCRN) to participate. Potentially eligible individuals will be identified from GP medical records by an electronic medical record search [21]. Potential participants will be recruited via their General Practitioner and a range of other methods as recommended by the pre-trial focus groups [22]:postal invitation letter including a summary of the study Participant Information Sheet and a full Participant Information Sheet or Participant Information Brochure for those interested;invitation letter including a summary of the study Participant Information Sheet on collection of repeat prescription;invitation during consultation with GP/Practice Nurse/Health Care Assistant at the practice;invitation to those eligible on registered research volunteer databasesposter present in the GP’s waiting roommedia campaign involving:
◦ local and national newspaper◦ radio◦ celebrity endorsement◦ publicity campaign using posters/leaflets

The study invitation letter will include a slip for participants to either express interest in finding out more about the study [23]. Those returning an expression of interest will be telephoned, more than 24 h after anticipated receipt of the Participant Information Sheet, by a member of the research team. The call will allow a discussion of the study, to answer any questions the potential participant may have, do a preliminary assessment of eligibility and if agreed, to make an appointment for a recruitment visit. An appointment letter/email will be sent out to confirm appointment. A reminder call/email or text, whichever is preferable to the participant, will be carried our 2 days prior to the screening appointment to reduce non-attendance [24]. Non-responders to the postal invite will be contacted by letter again once or via a message on the right side of a repeat prescription [25]. Those returning an expression of interest will be sent a full information sheet and dealt with as above.

#### Initial consultation

The following procedures will be undertaken in the order given below:obtain consenttake bloods from all consented participantscomplete study questionnairerandomise to treatment arm

### Administration of the test

After randomisation, all participants will be asked if they still wish to take part in the trial and still agree for their bloods to be used for the test and for future cancer related research. For participants randomised to the intervention arm the EarlyCDT®-Lung test will be performed and patients followed up according to their result (see Additional file 1: study flowchart).

At the initial visit, participants are told that those with a positive EarlyCDT®-Lung Test result will be invited to a follow-up visit to discuss the test results and explain what happens next. Those with a negative EarlyCDT®-Lung Test result will receive a letter explaining the test results and will be offered a follow-up visit or a telephone call if they wish. They will be told that the best way to reduce risk of developing lung cancer is by stopping smoking and that symptoms to watch for include persistent cough, coughing up blood, shortness of breath, weight loss or loss of appetite.

Those in the control arm will be written to and thanked for their contribution to the study and advised and counselled identically to those in the intervention arm who have had a negative EarlyCDT®-Lung Test result.

A patient specific section of the study website (www.eclsstudy.org) containing Participant Information Sheets and research staff contact details will be available for participants.

### Management of the visits

Based on the test’s reported 90% specificity and 41% sensitivity we anticipate that 520–550 participants in the intervention arm will have a positive test result. These will be offered a chest X-ray in accordance with local requirements for prioritisation and will be referred for a non-contrast thoracic CT scan. If there is a suspicious opacity on the chest X-ray or initial CT scan a contrast enhanced staging CT will be undertaken. As a quality control measure no participant undergoing CT screening in the test positive arm will have all their 5 CTs reported by same radiologist. Nodule size will be currently reported as the mean of 2 diameters at 90° angles, volumetric analysis is starting soon on both sites with diameter and volume to be reported. If the initial CT scan reveals no evidence of lung cancer then subsequent CT scans will be offered 6 monthly for 24 months. An appointment window of ± 4 weeks will be initiated for each scheduled CT scan.

If a test positive participant has had a chest X-ray in the previous 1 month, or a CT scan in the previous 3 months, these can be reviewed as part of the study. With the participant’s consent chest X-rays or CT scans prior to study entry will be retrospectively coded. The participant will proceed to have the series of up to 5 CTs.

Participants will receive appointments via post/email, according to patient preference. Participants will be called 2–4 days before each CT scan appointment. Individuals with abnormalities as classified by the radiology/respiratory physician’s study panel on baseline CT scan or subsequent CT scan will be followed up over the study period or referred for NHS clinical care as appropriate. All individuals entering the study will be flagged and followed-up via the Scottish Cancer Registry in the Electronic Data Research and Innovation Service (eDRIS) [26]. Participants who develop lung cancer will be followed-up via their medical records to assess both time to diagnosis and stage of disease at diagnosis. If no histological stage is available, stage will be assessed by a panel of three respiratory physicians blind to allocation status of the study subjects from chest X-rays or CT, or if no imaging is available, medical assessment of stage will be carried out.

Prior to sending CT scan appointment dates, the Scottish Community Health Index national register will be checked for vital status. All participants in the test- Positive test groups known to have died will be removed from the CT scan appointment schedule register. If patients (positive test) fail to attend for any imaging assessment during the study, they will receive two reminders (one letter, one phone call). On the third non-attendance, a letter will be sent to the participant’s GP to inform them of non-attendance.

Participants will receive results letters in relation to their initial chest X-ray and CT scan and subsequent CT scans. Any clinical intervention/treatment will be arranged by the relevant NHS multidisciplinary team.

### Control

The comparator is UK standard clinical practice which involves awaiting the development of symptoms and investigation of those symptoms according to national guidelines [27, 28].

### Intervention

EarlyCDT®-Lung Test blood sample followed by X-ray and serial cross sectional CT imaging in those with a positive result 6 monthly for 24 months. Those with a negative test, like the controls, have no further investigations but are provided with standard clinical care.

### Outcomes

#### Primary

The difference, at 24 months after randomisation, between the rates of patients with stage III, IV or unclassified lung cancer at diagnosis in the intervention arm, and those in the control arm;

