*Baseline Questionnaire*	X				
*Thank you letter to Control Group*		X			
*EarlyCDT- Lung Test Result Letter*		X			
*GP Results Letter & ICF copy (negative)*		X			
*Result Discussion/ Imaging Schedule*			X		
*Provide PIS 2*			X		
*GP Result Letter & ICF copy (positive)*			X		
EarlyCDT – Lung Test Positive Result Participants – Imaging Schedule					
	Timeline(± 12 weeks)				
	0	6 months	12 months	18 months	24 months
*CXR*	X				
*CT Scan*	X	X	X	X	X
*Scheduled every 6 months, if participant enters NHS clinical care pathway, subsequent study CT scans will be cancelled.*		*Research team member will call 2–4 days before each scheduled CT scan to check health status and attendance.*			

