### Proposed analyses

Characteristics of participants will be compared informally between treatment arms at baseline. The main analysis of the primary outcome will be intention-to-treat. Cox proportional hazards models which will be used to estimate the hazard ratio of the rate of late stage lung cancer in the intervention arm compared to the control arm. Participants who are lost to follow up will be censored. The models will adjust for age, gender smoking history, socioeconomic status and practice. If appropriate, random cluster effects will be included rather than fixed effects for practices. A similar methodology will be used for the secondary outcomes of comparisons of mortality rates. A subsequent analysis will compare the outcomes of those with a positive test in comparison to those in the intervention group with a negative test (primary contrast for this analysis) and those in the control group. Comparisons of proportions will be carried out using chi square tests. Fisher’s exact test will be used if the number of events is small.

Psychological and behavioral outcomes will be compared between the three groups (Test-positive, Test-negative and the control group) at baseline using analysis of variance (or non-parametric tests if there is evidence of non-normal distribution of scores) for continuous measures and *χ*
^2^ tests for categorical measures. Psychological (HADS Score) and behavioral measures will be described at each follow up time point and multilevel regression models will be used for analyses to take account of repeated measurements during follow up [38].

Poisson regression models, adjusting for follow up time if necessary, will be used to investigate the other clinical measures (secondary outcomes 7 and 8).

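### The primary outcome is a difference in late-stage rates at 24 months, but the primary analysis is a Cox hazard ratio with no stated 24-month horizon and no absolute difference

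*Protocol article*

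**What the plan says.** Outcomes – Primary sets the outcome as "The difference, at 24 months after randomisation, between the rates of patients with stage III, IV or unclassified lung cancer at diagnosis", comparing the intervention arm with the control arm.

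Proposed analyses states "The main analysis of the primary outcome will be intention-to-treat", using "Cox proportional hazards models which will be used to estimate the hazard ratio of the rate of late stage lung cancer in the intervention arm" relative to control, with adjustment for age, gender, smoking history, socioeconomic status and practice. The only censoring rule given is "Participants who are lost to follow up will be censored". A general line adds "Comparisons of proportions will be carried out using chi square tests", with Fisher's exact test for small numbers, but it is not attached to the primary outcome.

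Sample size calculations – Main study gives the target as a 35% relative reduction and assumes exponential survival. The revised calculation takes a control rate of 600 per 100,000 per year, 12,000 participants and recruitment over 2 years, with analysis once everyone has 2 years of follow-up. It states 80% power. The imaging schedule in Table 1 runs from 0 to 24 months.

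**The concern.** The outcome has a scale (a difference) and a time (24 months). The stated analysis fixes neither.

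Scale: a hazard ratio does not give the absolute difference unless the control rate is known. The protocol calls that rate uncertain and has already halved it, from 1,200 to 600 per 100,000 per year.

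Time: with 2-year recruitment and analysis when the last participant reaches 2 years, follow-up at analysis runs from 2 to 4 years. Unless the Cox model is cut at 24 months, events in years 3 and 4 enter the primary estimate, although scanning in test-positive participants has by then ended and the contrast between arms may have changed. The reported hazard ratio could then be read as the 24-month effect when it is something else.

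**Working it through.** **Inputs.** From Sample size calculations – Main study: control rate 0.006 per year, hazard ratio 0.65 (so 0.0039 per year in the intervention arm), 6,000 per arm, 2-year recruitment (taken as uniform), minimum follow-up 2 years, two-sided 5%. The hazard patterns in step 4 are assumptions, as the documents give none.

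**1. The protocol's own power.**
- With everyone followed for exactly 2 years, expected events per arm are 6,000 × (1 − e^(−2r)). With 2-year accrual, this is averaged over follow-up times of 2 to 4 years.
- All follow-up counted: 107.0 + 69.8 = 176.8 events. By Schoenfeld, √176.8/2 × |ln 0.65| = 2.86, and 2.86 − 1.96 gives power of 81.7%. Freedman's formula and the comparison of proportions both give 80.5%. The stated 80% is reproduced.
- Cut at 24 months: 71.6 + 46.6 = 118.2 events. By Schoenfeld, √118.2/2 × |ln 0.65| = 2.34, giving 64.9%. Freedman gives 63.5% and proportions 63.6%.
- The initial calculation (5,000 per arm, 1,200 per 100,000 per year) does reproduce at a fixed 24 months: 196 events and 84.4–85.4% against the stated 85%. The horizon behind the power figure therefore lengthened at the revision, while the outcome stayed at 24 months.

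**2. The named outcome at planning values.**
- Control 2 × 0.006 × 6,000 = 72 events; intervention 0.65 × 72 = 46.8.
- Difference = 72/6,000 − 46.8/6,000 = 0.0120 − 0.0078 = 0.0042.
- SE = √(0.0120 × 0.9880/6,000 + 0.0078 × 0.9922/6,000) = 0.00181.
- 95% CI = 0.0042 ± 1.96 × 0.00181, that is 0.07 to 0.77 percentage points. Exponential risks (1.19% and 0.78%) give almost the same difference, 4.16 per 1,000.

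**3. What a hazard ratio of 0.65 means in absolute terms.** The 24-month difference is 2.1, 3.75, 4.2 or 8.2 per 1,000 at control rates of 300 (assumed), 540, 600 or 1,200 per 100,000 per year.

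**4. Does the Cox hazard ratio recover the 24-month relative effect?** The expected Cox estimate was solved under hazard ratios assumed for months 0–6, 6–12 and 12–24, each averaging 0.65 over 24 months.

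| Assumed pattern | 24-month risk ratio | Cox HR, cut at 24 months | Cox HR, 2–4 years, equal hazards after 24 months |
|---|---|---|---|
| 1.3 / 0.5 / 0.4 | 0.652 | 0.651 | 0.767 |
| 1.0 / 0.6 / 0.5 | 0.652 | 0.651 | 0.767 |
| 2.0 / 0.3 / 0.15 | 0.653 | 0.653 | 0.768 |

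The 0.767 can be checked by counting. Events after 24 months in controls are 107.0 − 71.6 = 35.4. With equal hazards the intervention arm has about 46.7 + 35.4 = 82.1, and 82.1/107.0 = 0.77. Power in these cases is about 44–45%. If instead a hazard ratio of 0.4 continues after 1.3 / 0.5 / 0.4, the count is 46.7 + 0.4 × 35.4 = 60.9 and the Cox estimate is 0.568. The estimate can move either way from the same 24-month effect.

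**The case against.** The best defence is that the word difference is used loosely throughout the list of outcomes, while the design target is relative. On that reading a hazard ratio is a natural primary measure, and demoting it would be a matter of preference. The first secondary outcome also counts stages at diagnosis by arm at 24 months, so a crude difference could be had by subtraction. An analysis plan, not shown here, may add absolute measures and checks of proportional hazards. Most of this stands: there is no case for demoting the hazard ratio, and missing diagnostics are not a fault of this article. It does not answer the horizon question. The article fixes 24 months in the outcome, omits it from the analysis, and states a power that needs later events.

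A reader might go further and infer that the screening schedule itself breaks proportional hazards and so invalidates the Cox analysis. There is a plausible route. The Background reports that "there was no difference in positivity rate for the test in early or late stage disease lung cancers", so the baseline CT could bring late-stage diagnoses forward, with any benefit coming later. But the documents do not show this. They give no prevalence of asymptomatic late-stage disease and no sojourn times. Only 520–550 of about 6,000 intervention participants (about 9%) are expected to test positive and be offered scans. Even a strong departure leaves a Cox hazard ratio cut at 24 months within 0.002 of the 24-month risk ratio.

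A reader might also infer that moving to a 24-month measure costs no power. Against the stated 80% it does.

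**Conclusion.** The mismatch is real and lies in the text: the named primary outcome is a 24-month difference, and the named primary analysis gives a ratio over an unstated period. On the relative scale it is of no practical consequence if follow-up is cut at 24 months. It is material if all follow-up is used: a 24-month risk ratio of 0.65 could appear as a hazard ratio of about 0.77, or about 0.57, depending on what happens after scanning ends. Those two values rest on assumed hazards and illustrate the range; they are not predictions. The power gap (about 64% against 80%) rests only on the protocol's own rates, sample size and accrual, with uniform recruitment and negligible loss to follow-up. The trial remains analysable, and the point should be settled before the primary analysis.

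**What to change.** - Report the difference between arms in 24-month cumulative incidence of stage III, IV or unclassified lung cancer, with its 95% CI, as the estimate of the named primary outcome, alongside the Cox hazard ratio. Treat death as a competing event.
- State whether the primary Cox model is cut at 24 months for every participant or uses all follow-up.
- If it is cut, restate the power as about 64% for a 35% reduction at 600 per 100,000 per year. If it is not, say that the hazard ratio covers 2 to 4 years and is not the 24-month effect.
- Optionally, add a rate ratio split at a prespecified time. It would be imprecise early on: at planning values months 0–3 hold about 72/8 = 9 control events.

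The cost is wording, a little code and one extra reported measure, with no new data. With a 24-month cut, the stated power becomes less favourable.
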